Its potential mechanism may be related to impairment of the function of GABAergic interneurons (Knoferle et al., 2014; Lenz et al., 2016; Wang et al., 2018). Many studies have suggested that the APOE4 allele can reduce the number and impair the function of GABA interneurons in the brain and increased cortical excitability (Knoferle et al., 2014; Lenz et al., 2016; Wang et al., 2018). This feature can also be confirmed by EEG results. High-frequency gamma oscillations are generally encoded by GABA interneurons in the brain (Traub et al., 2003; Colgin et al., 2009; Buzsaki and Wang, 2012; Gillespie et al., 2016). Inhibition of this neuronal activity can lead to a reduction in gamma oscillations, and the reduction of gamma oscillations in the brain of APOE4 carriers (Traub et al., 2003; Colgin et al., 2009; Buzsaki and Wang, 2012; Gillespie et al., 2016) is closely related to the symptoms of AD (Zhao et al., 2018; Etter et al., 2019; Najm et al., 2019). Transcranial magnetic stimulation can improve gamma oscillation power and amplitude, and improve cognitive function (Barr et al., 2009). These results suggest that the damage to gamma oscillation activities caused by the APOE4 allele may affect the treatment results. In summary, it is clear that the APOE genotype determines the number and function of GABAergic neurons in AD patients, and therefore may be related to the heterogeneity of transcranial magnetic stimulation effects. Considering this background, transcranial magnetic stimulation treatment protocols being implemented should vary with APOE genotypes.

Previous studies have tested the effect of both high-frequency rTMS (HF-rTMS) and low-frequency rTMS (LF-rTMS). Interestingly, it was found that both HF-rTMS of the left dorsolateral prefrontal cortex (L-DLPFC) and LF-rTMS of right dorsolateral prefrontal cortex (R-DLPFC) exhibited significant therapeutic efficacy (Chou et al., 2020). Additionally, Ahmed et al. (2012) reported that LF-rTMS of L-DLPFC also showed significant therapeutic efficacy for mild to moderate dementia. But there are no uniform guidelines or standards to guide the choice of treatment protocol. In terms of experience, most doctors will choose high frequency as the treatment scheme. The present study will adopt the left dorsolateral prefrontal cortex (L-DLPFC) as the intervention target.

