We believe that different APOE4 carriers should be given different treatment schemes than non-APOE4 carriers because of the excitability of their neural networks is different. The APOE4 carriers have increased network excitability due to the impairment of GABAergic interneuron function (Najm et al., 2019). Compared with the APOE ε3 allele, APOE ε4 allele increases Ca^2+^ excitability due to lysosome dysregulation and impaired modulation of Ca^2+^ responses upon changes in extracellular lipids (Larramona-Arcas et al., 2020). Traditional theory suggests that high-frequency rTMS increases cortical excitability by inducing long-duration enhancement potentials, while low-frequency rTMS decreases cortical excitability by inducing long-duration inhibition potentials (Pell et al., 2011). GABAergic neuronal receptor activity is mainly associated with chloride channel opening (Traub et al., 2003), and high-frequency stimulation is more likely to induce long-term potentiation (LTP) (Pell et al., 2011). Hence, high-frequency treatment contributes to more gamma oscillatory activity and better therapeutic effects. However, for APOE4 carriers with more significant loss of GABAergic neurons (Knoferle et al., 2014; Najm et al., 2019), HF treatment may be less effective. In this case, low-frequency therapy may be more suitable for that kind of patients. Therefore, in this study, it is believed that different transcranial magnetic stimulation regimens should be selected for AD patients based on APOE genotypes, so as to obtain precise treatment strategies.

In summary, this paper aims to study the difference in the efficacy of different rTMS strategies in AD patients with different APOE genotypes, and analyze the changes of gamma oscillations.

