## Objectives

The primary objective of the study is to analyze the different efficacies of rTMS in AD patients with different APOE genotypes, so as to provide the basis for the precise treatment of AD.

The secondary objective is to analyze the changes in gamma oscillations and pathological indicators in different APOE genotypes, thus being conducive to the precise treatment of AD.

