### EEG Acquisition and Calculation and Analysis of EEG Metrics

EEG data will be collected via a high-density 32-channel EGI system (g.tec) with a sampling rate of 500 Hz and a mastoidea reference. During the recording, patients are instructed to stay awake, relax, and close their eyes for 10 min. Then, a bandpass filter (from 0.5 to 200 Hz) and a notch filter at 50 Hz and 100 Hz were applied. In addition, EEG will be collected under the condition of eyes closed, followed by preprocessing via MATLAB software, such as baseline adjustment, filtering, depression filtering, and referring. Finally, the changes in EEG power and spectra in different frequency bands before and after treatment of different genotypes were analyzed and compared.

EEG metric data will be processed and analyzed by MATLAB 2017. Beyond that, power spectral density (PSD), median spectral frequency (MSF) and spectral entropy measure dynamics of brain signals at a single electrode site are based on spectral frequency content.

For the main analysis, 10 EEG metrics: PSD in delta (1–4 Hz), theta (4–8 Hz), alpha1 (8–10 Hz), alpha2 (10–13 Hz), beta 1(13–20 Hz), beta 1(20–30 Hz), gamma1 (30–48 Hz), and gamma1 (48–100Hz) will be calculated, and then averaged across all epochs (60 s recording).

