### Biomarker Test of Blood Samples

Aβ1-42, Aβ1-40, p-tau217 and other indicators of the plasma were detected by liquid phase flow cytometry (using the MSD platform) before and after treatment to evaluate the outcome of pathological indicators. Specifically, blood samples were collected at 7:00 a.m. before and after treatment, and plasma samples were obtained after centrifugation for MSD detection.

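### The only contrast named for the gamma objective is before-after change between APOE genotypes; it leaves out HF versus LF, the sole randomised factor

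*Protocol article*

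**What the plan says.** The Objectives section sets the secondary objective: to "analyze the changes in gamma oscillations and pathological indicators in different APOE genotypes". The EEG section turns this into an analysis, in which "the changes in EEG power and spectra in different frequency bands before and after treatment of different genotypes were analyzed and compared". Neither sentence mentions stimulation frequency.

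The section on blood biomarkers says only that plasma markers are measured "before and after treatment to evaluate the outcome of pathological indicators". It names no contrast, by genotype or by arm, so the link between plasma markers and genotype comes from the Objectives section alone.

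Elsewhere the design is built around frequency. Under Randomization and Allocation, patients are randomised to HF or LF within genotype strata, 24/24 in carriers and 16/16 in non-carriers. The Statistical Hypothesis section sets HF over LF as the trial hypothesis with MMSE as its indicator, and orders the HF-LF comparison first in non-carriers and then in carriers. The Introduction argues that the regimen should be chosen by genotype. It reasons that "high-frequency treatment contributes to more gamma oscillatory activity and better therapeutic effects", that HF may work less well in carriers, and that LF may suit them better.

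**The concern.** The mechanistic argument concerns how frequency and genotype act together. The contrast written for gamma uses genotype alone, so randomisation plays no part in it. A difference between carriers and non-carriers in two-week EEG change could come from stimulation. It could equally come from a different baseline EEG, regression to the mean, or anything else that differs by genotype. A finding of no difference would be just as hard to read, because a real HF-LF effect shared by both genotypes cannot appear in this contrast. Neither result would say which frequency suits which genotype, which is the question the Introduction raises.

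The article already shows how such a comparison can be over-read. In Results in Progress, cognitive change is compared by genotype with the arms combined, which is understandable while allocation is concealed. The Abstract and Discussion then conclude that the two groups should be treated differently. The EEG sentence sets up the same kind of comparison for gamma.

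**Working it through.** **Stated figure.** The article gives no effect size, SD or power for EEG or plasma markers. Its only power figure is for MMSE, 81% with 13 and 12 per group. With the stated SDs taken as known, SE = √(1.9²/13 + 2.3²/12) = 0.848 and power = Φ(2.4/0.848 − 1.96) = 80.8%, so the figure reproduces. It has no bearing on the EEG contrast.

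**What the written contrast estimates.** Let c_HF, c_LF, n_HF and n_LF be the mean changes in carriers (c) and non-carriers (n). With 1:1 arms inside each stratum and no separation by arm, the genotype contrast is

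G = (c_HF + c_LF)/2 − (n_HF + n_LF)/2.

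- Common frequency effect (HF adds a and LF adds b in both genotypes): G changes by (a + b)/2 − (a + b)/2 = 0, whatever the size or sign of a and b.
- Symmetric crossover (carriers −d under HF and +d under LF, non-carriers the reverse): G = 0 − 0 = 0.
- HF acts only in non-carriers, by D, and LF does nothing: G = 0 − D/2. Its size is half the HF-LF difference D in non-carriers.

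**Illustration from the planning values (Sample Size Calculation).** MMSE changes are 11.2 − 10.4 = +0.8 under HF and 8.8 − 10.2 = −1.4 under LF, a difference of 2.2. Averaged 1:1 they give (0.8 − 1.4)/2 = −0.3. If this held in both genotypes, G would be 0.

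**Standard errors, in units of the within-cell SD of change, at 24/24/16/16 with no losses.**
- Genotype contrast: √(1/48 + 1/32) = 0.228 (slightly more when the combined arms differ in mean)
- HF − LF in carriers: √(2/24) = 0.289
- HF − LF in non-carriers: √(2/16) = 0.354
- HF − LF overall, strata weighted 0.6 and 0.4: √(0.36 × 2/24 + 0.16 × 2/16) = 0.224
- Interaction: √(2/24 + 2/16) = 0.456

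**Power, two-sided 5%, normal theory.** The cell effects below are assumptions in SD units. In each cell of the table the contrast comes first, then its power; the genotype SE allows for the extra spread from combining arms.

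| Assumed change HF/LF: carriers; non-carriers | Genotype | HF−LF overall | HF−LF carriers | HF−LF non-carriers | Interaction |
|---|---|---|---|---|---|
| +0.5/−0.5; +0.5/−0.5 | 0, 5% | 1.0, 99% | 1.0, 93% | 1.0, 81% | 0, 5% |
| +0.5/0; +0.5/0 | 0, 5% | 0.5, 61% | 0.5, 41% | 0.5, 29% | 0, 5% |
| −0.5/+0.5; +0.5/−0.5 (crossover) | 0, 5% | −0.2, 14.5% | −1.0, 93% | 1.0, 81% | −2.0, 99% |
| 0/0; +1/0 | −0.5, 53% | 0.4, 43% | 0, 5% | 1.0, 81% | −1.0, 59% |
| 0/−0.5; +0.5/−0.5 | −0.25, 17% | 0.7, 88% | 0.5, 41% | 1.0, 81% | −0.5, 19.5% |

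In the first three rows the written contrast has no more than its 5% error rate, while at least one randomised contrast carries the effect. In the last two it keeps part of the signal. The interaction is no cure-all: in the last row its power is hardly better than that of the genotype contrast.

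**The case against.** The strongest reply is that pooling is nowhere written. The EEG sentence is one condensed line in a journal article. The Statistical Analysis Methods section offers between-group tests and repeated-measures ANOVA without defining the groups, which could include HF versus LF. The Introduction's closing aim mentions different rTMS strategies and gamma together. EEG and plasma measures are not among the listed outcomes, and details for such measures are commonly left to an analysis plan. It is also true that a genotype comparison answers the secondary objective as literally worded.

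Much of this stands. Pooling is an inference from silence about the arms. The point survives because the article is not silent about the contrast: it names one, twice, and it is not the randomised one, whereas for MMSE it does name HF versus LF.

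A reader might go further and infer that the arms are expected to push gamma in opposite directions, so that the effect must cancel. The documents do not support that:
- Opposite directions are stated for cortical excitability only: "high-frequency rTMS increases cortical excitability by inducing long-duration enhancement potentials", while "low-frequency rTMS decreases cortical excitability by inducing long-duration inhibition potentials". Nothing says LF lowers gamma, and the Introduction also says that "Transcranial magnetic stimulation can improve gamma oscillation power and amplitude" without distinguishing frequency.
- No direction by arm is given for any plasma marker.
- Cancellation is exact only for a common frequency effect or a symmetric crossover. The article's own reasoning, that HF may work less well in carriers, also allows patterns in which the genotype contrast is diluted but not zero.

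Nor does the biomarker section contain a genotype comparison that could be called wrong; it names no contrast.

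**Conclusion.** The point holds in limited form. For gamma, the article fixes a between-genotype contrast that does not use the randomisation and does not address choice of frequency by genotype. Under the planned 1:1 allocation it cannot show a frequency effect common to both genotypes or a symmetric crossover. Other frequency-by-genotype patterns are weakened, by half where HF acts only in non-carriers and LF has no effect.

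The algebra assumes that the arms are combined within genotype and stay balanced among the patients analysed. The power figures also rest on assumed SD-unit effects and no losses; they show the pattern and do not predict this trial's results. Opposing effects on gamma or plasma markers remain an assumption. The matter concerns a secondary, mechanistic objective and leaves the MMSE analysis and the sample size untouched. It should be corrected because it decides what the EEG results can be said to show.

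**What to change.** In the EEG section, state the contrast as the HF-minus-LF difference in change from baseline in gamma power, estimated within carriers and within non-carriers, together with the frequency-by-genotype interaction (the difference between those two differences). Apply the same contrasts to the plasma markers covered by the secondary objective; in the biomarker section this adds a contrast where none is named. Word the secondary objective to match. Keep before-after change by genotype as a descriptive summary, labelled as a comparison of non-randomised groups.

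The change is to wording. EEG and blood sampling are already planned for all patients in all four cells. The article reports 18 of 80 patients included and allocation not yet unblinded, so on that account the contrast can be fixed before arm-level results are seen.

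The cost is precision: the interaction's standard error is 0.456/0.228 = 2.0 times that of the genotype contrast, and the within-genotype HF-LF contrasts have standard errors of 0.289 and 0.354 SD. The interaction should therefore be reported as an estimate with its confidence interval, and a non-significant result should not be read as showing that genotype makes no difference.

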### Outcomes

The primary end point is the quantitative index, namely MMSE, whereas the secondary outcome measures are MoCA, ADAS-cog, GAD-7, CES-D, and ADL.

### Sample Size Calculation

The sample size of this project was calculated by Pass software on the basis of previous literature. In this study, the MMSE scores of the HF-rTMS group and the LF-rTMS group were 10.4 ± 1.7 and 10.2 ± 1.8, respectively, before treatment. After 2 weeks of rTMS treatment, their MMSE scores reached 11.2 ± 1.9 and 8.8 ± 2.3, respectively (Ahmed et al., 2012), when the target effect size had 80% power (β = 0.10) and a type I error was 5% (α = 0.05). In addition, the group sample size of 13 and 12 achieved 81% power for detecting a difference of 2.4 between the null hypothesis and that the mean of both groups is 11.2 and the alternative hypothesis that the mean of Group 2 is 8.8 with known group standard deviations of 1.9 and 2.3 and a significance level (alpha) of 0.050 using a two-sided two-sample *t*-test, while the sample size of each subgroup is at least 13. Considering the loss of follow-up, falling off and sample data being eliminated due to data quality, the sample size should be increased by 20%. Thus, the final sample size of each subgroup are at least 16. Furthermore, the ratio of APOE4 carriers to non-APOE4 carriers are set to 3:2 according to the comparison of population samples and our previous study. Other than that, in this study, 80 participants, with 48 APOE4 carriers and 32 non-APOE4 carriers will be recruited.

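### The sample size paragraph pairs 80% power with a beta of 0.10, and labels as a t-test an 81% power that holds only for a normal test with known SDs (t-test: about 78%)

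*Protocol article*

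**What the plan says.** All of the power statements stand in one paragraph of the protocol article, Sample Size Calculation.

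- **Target.** "the target effect size had 80% power (β = 0.10) and a type I error was 5" per cent.
- **Result.** "the group sample size of 13 and 12 achieved 81% power for detecting a difference of 2.4" MMSE points, that is, post-treatment means of 11.2 and 8.8.
- **SDs.** The calculation is made "with known group standard deviations of 1.9 and 2.3".
- **Test.** It uses "a significance level (alpha) of 0.050", "using a two-sided two-sample" t-test.
- **Minimum and allowance.** The paragraph takes 13 as the minimum per subgroup. To cover loss to follow-up, dropout and data removed for quality, it says that "the sample size should be increased by 20" per cent, and arrives at 16 or more per subgroup.

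Stratified Randomized Groups then assigns 16 patients to each non-carrier arm and 24 to each carrier arm, 40 per frequency overall. Statistical Analysis Methods names the independent-sample t-test for comparing normally distributed measures between groups.

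**The concern.** Two statements conflict with others in the same paragraph. First, 80% power and a beta of 0.10 cannot both hold, since a beta of 0.10 is 90% power. Second, a t-test estimates the SD from the data, whereas a calculation with known SDs is a normal (z) test. At about a dozen patients per group the two differ by about three percentage points, enough to move the result from just above the 80% target to just below it.

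This paragraph is the only justification given for the sample size, and it concerns the primary measure, MMSE. Statistical Hypothesis puts the non-carrier comparison first in its ordered subgroup testing, and the non-carrier arms are the smallest. The power quoted for a group of this size should therefore be that of the test that will be run.

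**Working it through.** **Inputs (Sample Size Calculation).** Difference 2.4; SDs 1.9 and 2.3; groups of 13 and 12; two-sided alpha 0.05. Arm sizes of 16 and 24 are from Stratified Randomized Groups.

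**1. The plan's figure, with SDs known.**
- SE = √(1.9²/13 + 2.3²/12) = √(0.2777 + 0.4408) = 0.848.
- 2.4 / 0.848 = 2.83.
- Power = Φ(2.83 − 1.96) = 80.8%, which is the stated 81%.

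**2. The stated minimum, with SDs known.**
- n per group = (1.96 + 0.842)² × (1.9² + 2.3²) / 2.4² = 12.1, rounded up to 13. This is a beta of 0.20.
- With a beta of 0.10, 1.282 replaces 0.842 and n = 16.2, rounded up to 17.
- So the stated 13 belongs to a beta of 0.20.

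**3. The same inputs as a t-test (noncentral t).**
- Pooled SD at 13 and 12 = √[(12 × 1.9² + 11 × 2.3²) / 23] = 2.10.
- Noncentrality = 2.4 / (2.10 × √(1/13 + 1/12)) = 2.85; critical value 2.069 on 23 df; power 78.0%.
- Welch version: noncentrality 2.83, about 21.4 df, power 77.1%.
- A simulation of 200,000 trials gave 77.8% and 76.8%.

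| Evaluable per arm | Known-SD z-test | Pooled t-test |
|---|---|---|
| 12 and 12 | 79.6% | 75.9% |
| 13 and 12 | 80.8% | 78.0% |
| 13 and 13 | 82.7% | 79.5% |
| 14 and 14 | 85.3% | 82.6% |
| 16 and 16 | 89.6% | 87.6% |
| 24 and 24 | 97.6% | 97.1% |

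For equal groups, 14 is the smallest size at which the t-test passes 80%. For 90% it would need 18 (91.2%; 17 gives 89.5%).

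**4. The allowance for losses.**
- As worded: 13 × 1.2 = 15.6, rounded up to 16. The plan's figure follows.
- If 20% of those enrolled were lost (an assumption, because the plan gives no loss rate): 16 × 0.8 = 12.8, so 12 to 13 remain per non-carrier arm and t-test power is 75.9% to 79.5%. Keeping 13 would need 13 / 0.8 = 16.25, rounded up to 17.
- Carrier arms: 24 × 0.8 = 19.2. At 19 and 19 the pooled t-test has 92.7% power.

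**The case against.** The case for leaving the paragraph alone is that its numbers can be rebuilt. It says openly that the SDs are taken as known, and on that premise 81%, 13 and 16 all follow. Nearly everything points to 80% as the target; only the beta symbol disagrees. The trial also enrols 16 and 24 per arm rather than 13 and 12, and both exceed the t-test minimum of 14 before losses. All of this stands. It limits the point to what is stated and leaves the design intact. It does not remove the point, because the beta is still wrong and the 81% is still attributed to a test that does not give it.

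Three stronger readings are tempting, and the documents do not support them.

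- **That the calculation cannot be reproduced.** It can, as a known-SD calculation. The fault lies in the label.
- **That the trial as a whole misses its stated power.** At the plan's own inputs the t-test has 87.6% power with 16 evaluable per arm, 97.1% with 24, and over 99% with 40. A shortfall below 80% can arise only in the non-carrier pair, and only if losses are near 20%.
- **That 16 is an arithmetic error for 17.** The plan speaks of an increase of 20%, not of a 20% loss rate, and its sum follows that wording. Read as a loss rate, the gap is one patient per non-carrier arm.

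**Conclusion.** The point holds as two misstatements and one minor omission.

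- **Beta.** A value of 0.10 beside 80% power is a plain contradiction. It should read 0.20. The error is confined to the text and did not drive the sample size.
- **Test label.** The 81% is a known-SD figure. For the t-test that the sentence names, power at 13 and 12 is 78.0% (pooled) or 77.1% (Welch), about three to four points lower. The stated minimum of 13 gives 79.5%, just under the target, so the t-test minimum is one patient per group higher.
- **Losses.** The allowance follows its own wording. What is missing is the power left in the non-carrier arms if a fifth of patients were lost: about 76% to 79%, against 87.6% with none lost.

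These figures rest on the plan's own means and SDs, normally distributed scores, two-sided alpha 0.05 and, for the last item only, an assumed 20% loss. Whether those means and SDs suit this population is a separate question, not examined here.

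**What to change.** In Sample Size Calculation:

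1. Change beta to 0.20.
2. Either give the power at 13 and 12 as about 78% for the two-sided two-sample t-test, or keep 81% and label it a known-SD z-test figure. In both cases give 14 per group as the t-test minimum for 80%.
3. Say what the 20% increase allows for, and give t-test power for the non-carrier arms of 16 over a range of losses: 87.6% with none lost, 82.6% with 14 left per arm (16 − 2, a 12.5% loss), and about 76% to 79% with 12 to 13 left.

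The cost is a few restated and slightly less favourable numbers. Enrolment, allocation and analysis stay as they are: 16 per arm still covers the t-test minimum of 14 if no more than two patients per arm are lost, and the carrier arms of 24 have ample margin.

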## Introduction

Alzheimer’s disease (AD) is a neurodegenerative disease characterized by memory loss and cognitive dysfunction, with a very high prevalence in the middle-aged and elderly population. In this context, hundreds of billions of dollars have been invested in related research and development worldwide, but unfortunately, there are still no drugs with proven efficacy. Moreover, patients may wander and lose their ability to live in the late stages, which is a heavy burden for society and families (Zhou et al., 2019). Therefore, investigating new treatments is urgently needed.

Repetitive transcranial magnetic stimulation (rTMS) is a safe, non-invasive, and inexpensive neuromodulation that can affect the synaptic plasticity of neurons and enhance brain function by adjusting parameters such as stimulation frequency and stimulation intensity (Bestmann, 2008). In recent years, some researchers have tried to adopt rTMS to treat Alzheimer’s disease and found that it has a better therapeutic effect (Dong et al., 2018; Chou et al., 2020). The current clinical treatment of Alzheimer’s disease with medications has unsatisfactory therapeutic effect. Zhang et al. (2020) reported a meta-analysis of pharmacological treatments showing that improvement of Mini-mental State Examination (MMSE) score standard mean difference (SMD) ranges from −0.29 to 0.49; Lu et al. (2020) also reported another analysis of anti- Aβ agents for mild to moderate Alzheimer’s disease suggesting no effect of anti- Aβ drugs vs. the placebo group (SMD of MMSE score improvement: −0.29, 95% CI −0.76–0.17; SMD of ADAScog score improvement: MD: 0.20, 95% CI: −0.40–0.81). In contrast, Chu et al. (2021) reported a promising result. The patients who received high-frequency TMS treatment had a significant improvement in MMSE score (1.65, 0.77–2.54) when compared with sham TMS. In addition, Dong et al. (2018) report also supported the viewpoint that high-frequency rTMS led to a significant improvement in cognition as measured by ADAS-cog (MD = −3.65, 95% CI −5.82 to −1.48). Although the results derived from different study samples, their subjects were AD patients. Although there are no studies designed to compare the differences in therapeutic effects between drugs and rTMS, these data point to the possibility that rTMS is superior to drug therapy of AD patients.

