**Inclusion criteria**

(1)The age ranges from 50 to 85 years old.(2)Subjective perception of memory loss more than 1 year; MMSE ≤ 26 (level of education more than 7 years: MMSE ≤ 26; level of education 1–7years: MMSE ≤ 24; level of education less than 1 year: MMSE ≤ 19).(3)MRI exhibits medial temporal atrophy (hippocampus, entorhinal cortex, amygdala); MTA visual evaluation scale ≥ 2.

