### Results in Progress

Our study is still in progress. Our current data are the preliminary data of the RCT study, and the grouping has not been unblinded. We analyzed the demographic informatics of APOE4 carriers and non-carriers and the changes in cognitive function scores before and after 2 weeks of rTMS treatment. More detailed information was displayed in Supplementary Table 1.

To date, 18 patients with clinically diagnosed Alzheimer’s disease have been included and have received rTMS treatment for 2 weeks. Among them, ten were APOE4 carriers; eight were non-carriers, and there were no significant differences in age, education or gender (Table 2). They were randomly assigned to the high-frequency treatment group or the low-frequency treatment group. Because the study was not blinded, we could not know which subgroup they were assigned to. We could only analyze the overall treatment effect. According to our preliminary results, there was no significant difference in MMSE score, MoCA score except ADAScog (Supplementary Table 1) score between the two groups before and after treatment. When comparing the improvement rate of the two groups, there was a significant difference in the improvement of MoCA score between the two groups. For non- carriers, the MoCA score but not the MMSE or ADAScog score improved by 2.65 ± 3.15, while for carriers, it improved by 0.1 ± 1.7 (*t* = 2.164, *p* = 0.046, Figures 2A–C).

**TABLE 2 T2:** Characteristics of the study cohort.

	APOE4 carriers (*n* = 10)	Non-APOE4 carriers (*n* = 8)	*p*-value
Sex F/M	6/4	5/3	0.914
Age, years	70.37.45	73.756.27	0.312
Education level, years	7.72.98	6.135.37	0.44
MMSE score before rTMS	12.66.77	15.888.54	0.377
MoCA score before rTMS	7.94.28	9.255.50	0.566
ADAScog score before rTMS	39.1316.49	34.8719.03	0.618
MMSE score after rTMS	13.56.22	16.638.73	0.388
MoCA score after rTMS	84.47	11.887.72	0.202
ADAScog score after rTMS	37.1616.39	31.5721.21	0.536

*n, number; F, female; M, male; MMSE, Mini Mental State Examination; rTMS, repetitive transcranial magnetic stimulation; MoCA, Montreal Cognitive Assessment Scale; ADAScog, Assessment Scale-cognitive subscale.*

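### The 81% power claim uses MMSE standard deviations of about 2, but the trial's own patients show 6 to 9; raw-score power at the planned sizes is about 12% in non-carriers, 26% in carriers and 30% overall

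*Protocol article*

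**What the plan says.** Sample Size Calculation takes post-treatment MMSE of 11.2 ± 1.9 (HF) and 8.8 ± 2.3 (LF) from one earlier study, whose baseline values were 10.4 ± 1.7 and 10.2 ± 1.8. It states that "the group sample size of 13 and 12 achieved 81% power for detecting a difference of 2.4", "with known group standard deviations of 1.9 and 2.3", at "a significance level (alpha) of 0.050 using a two-sided two-sample *t*-test". It takes 13 as the minimum per subgroup and adds 20% for losses, giving 16. Randomization and Allocation then plans 24 per arm in carriers, 16 per arm in non-carriers and 40 per arm overall.

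The Inclusion criteria ask for "Subjective perception of memory loss more than 1 year; MMSE ≤ 26", with lower ceilings for patients with less education and no floor. Table 2 (Results in Progress) reports MMSE in the first 18 patients, 10 carriers and 8 non-carriers, including the row "MMSE score before rTMS".

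Statistical Hypothesis states overall superiority of HF over LF. For the subgroups, HF and LF are compared first in non-carriers, and in carriers only if that P-value is below 0.05.

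**The concern.** The planning SDs describe a group of patients clustered near MMSE 10. The entry criteria allow a far wider spread, and the article prints the evidence of that spread without returning to the sample size. Power falls steeply as the SD rises for a fixed difference, so the 81% may not describe this trial.

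The order of testing adds to the problem. Non-carriers have the fewest patients and the largest observed SD, and the carrier comparison depends on their result. If the first test has little power, the genotype-specific question behind the trial may never formally be reached in carriers.

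**Working it through.** **1. The plan's own figure.** With SDs treated as known, power = Φ(d/SE − 1.96).
- SE = √(1.9²/13 + 2.3²/12) = 0.848
- 2.4/0.848 = 2.83, and Φ(2.83 − 1.96) = 80.8%

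The stated 81% reproduces. A t-test with estimated SDs gives 77%. The arithmetic is sound, so the question is the SD input.

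**2. Reading Table 2.** Mean and spread are run together in the available text. The reading is: carriers 12.6, 6.77 before and 13.5, 6.22 after; non-carriers 15.88, 8.54 before and 16.63, 8.73 after. Two-sample t-tests with these spreads as SDs give p = 0.376 and 0.387, against the printed 0.377 and 0.388. Treated as standard errors they give about 0.76–0.77. They are SDs.

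**3. Precision of those SDs.** The chi-square 95% interval for an SD is √[(n−1)s²/χ²].
- Post-treatment, carriers (n = 10): 4.3 to 11.4
- Post-treatment, non-carriers (n = 8): 5.8 to 17.8

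Both exclude 1.9 and 2.3. The arms are pooled within genotype, but removing a 2.4-point arm difference changes the SDs only to 6.10 and 8.65. Against the average planning SD of 2.11, the ratios are 6.22/2.11 = 2.9 and 8.73/2.11 = 4.1.

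**4. Power on raw post-treatment MMSE.** Difference 2.4, two-sided 0.05, noncentral t with noncentrality 2.4/(SD·√(2/n)). The pooled SD is √[(9×6.22² + 7×8.73²)/16] = 7.42.

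| Comparison | n per arm | SD | Noncentrality | Power |
|---|---|---|---|---|
| Size used in the calculation | 13 | 6.22 | 0.98 | 16% |
| Size used in the calculation | 13 | 8.73 | 0.70 | 10% |
| Non-carriers as planned | 16 | 8.73 | 0.78 | 12% |
| Carriers as planned | 24 | 6.22 | 1.34 | 26% |
| Overall | 40 | 7.42 | 1.45 | 30% |
| Overall, SD range | 40 | 6.22 to 8.73 | 1.73 to 1.23 | 40% to 23% |

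At the lower confidence limit of the carrier SD (4.28), power with 13 per arm is 28%.

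**5. Power with baseline adjustment.** The residual SD is SD·√(1−r²). The MMSE pre-post correlation r is not reported, so it is assumed. As a guide, the MoCA figures in Results in Progress imply r = (s₀² + s₁² − s_change²)/(2·s₀·s₁):
- Non-carriers: (5.50² + 7.72² − 3.15²)/(2×5.50×7.72) = 0.94
- Carriers: (4.28² + 4.47² − 1.7²)/(2×4.28×4.47) = 0.93

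Power for 2.4 points, each stratum's own post-treatment SD, no dropout (residual SD in brackets):

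| Assumed r | Non-carriers, 16 per arm | Carriers, 24 per arm | Overall, 40 per arm |
|---|---|---|---|
| 0.8 | 24% (5.24) | 59% (3.73) | 66% (4.45) |
| 0.9 | 41% (3.81) | 85% (2.71) | 91% (3.24) |
| 0.93 | 53% (3.21) | 95% (2.29) | 97% (2.73) |

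If non-carriers fall to 13 per arm, the 53% becomes 45%.

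**The case against.** **Pre-post correlation.** The strongest reply is that the low figures hold only for an unadjusted comparison of post-treatment scores. Statistical Analysis Methods also lists repeated-measures ANOVA, and if MMSE is as stable as MoCA over 2 weeks, carriers and the overall comparison could exceed the claimed 81%. This stands. It would be wrong to infer that every planned comparison has 10–16% power: that range belongs to 13 per arm on raw scores. But the calculation itself uses raw scores. The correlation comes from another scale over 2 weeks, whereas Statistical Hypothesis includes the 3-month follow-up in the MMSE endpoint. The non-carrier test stays below 80% across the range shown.

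**Small numbers.** Table 2 rests on 10 and 8 patients. That widens the answer but does not rescue the planning SDs, which lie outside both intervals.

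**Stronger readings that the documents do not support.**
- A reader might infer that the cited sample had severe dementia. The article never says so. Its Introduction reports that "LF-rTMS of L-DLPFC also showed significant therapeutic efficacy for mild to moderate dementia", citing the same study. Only a narrow sample with baseline MMSE near 10 is supportable.
- A reader might infer that 2.4 points is shown to be too large, because the Introduction reports that "The patients who received high-frequency TMS treatment had a significant improvement in MMSE score" of 1.65 against sham. That is HF versus sham, not HF versus LF, and its interval (0.77–2.54) contains 2.4. The 1.4-point LF decline built into the 2.4 (10.2 to 8.8) sits awkwardly with the cited LF efficacy, but that is a separate consistency question.
- A reader might expect a null result to be reported as no difference between frequencies. The article plans only a superiority test and says nothing of the kind.

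**Conclusion.** The concern holds as a fault in an input assumption, not in the arithmetic. The 81% is reproducible only with SDs that the trial's own data exclude. On the measure used in the calculation, power for 2.4 points at the planned sizes is about 12% in non-carriers, 26% in carriers and 30% overall (23–40%). These figures assume the Table 2 SDs, no dropout and no baseline adjustment.

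With adjustment, the answer depends on an unreported correlation. For r from 0.8 to 0.93, power is 24–53% in non-carriers, 59–95% in carriers and 66–97% overall. The mismatch in SDs is well established; any single replacement power figure is not. The practical weakness lies in the non-carrier comparison, which is under-powered throughout this range and decides whether carriers are tested.

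**What to change.** - Keep 80 patients and withdraw the 81% figure.
- State that the HF–LF comparison of MMSE is adjusted for baseline MMSE (ANCOVA). Baseline MMSE is already collected.
- Restate power and the detectable difference for non-carriers, carriers and overall, from the blinded MMSE SDs in each stratum and over a range of pre-post correlations, with and without the 20% allowance for losses. One pooled SD and one correlation for both strata would flatter the non-carrier test.
- Report the blinded MMSE pre-post correlation from the patients already treated, so that the range can be narrowed.
- In the same paragraph, correct "the target effect size had 80% power (β = 0.10": 80% power corresponds to β = 0.20.

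The cost is a rewritten paragraph and a less favourable stated power, most visibly in non-carriers. No extra patients, visits or unblinding are needed.
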